### Descriptive Statistics

Data will be cleaned, the descriptive statistics of the sample will be assessed, and all variables will be checked for normality of distribution. Descriptive statistics of our sample will be calculated to summarize demographic and disease-related characteristics and check for group differences between groups using Chi-squared and *t* tests. In case data are nonnormal, the Kenward-Roger correction for degrees of freedom will be applied to the LMM. Potential treatment moderators of age, sex, cancer type, cancer stage, and chemotherapy regimen will also be included as possible covariates. We will also conduct correlation and regression analyses to determine correlations between scores of the primary and secondary outcome measures, eg, correlation between C-SOSI and PROMIS-Cancer Anxiety scores, and between secondary outcome measures, eg, correlation between PROMIS-Cancer Fatigue scores and mood words selected by the participant in the *Am* app.

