### Sample Size

In previous studies with face-to-face group MBCR, we have observed medium effects for symptoms of stress (measured by the Calgary Symptoms of Stress Inventory [C-SOSI]) as the primary outcome and expect similar effects in this study. Also, recent meta-analyses of MBIs and psychosocial stress outcomes have demonstrated a similar medium standardized effect size of Cohen *d*=0.5 for stress [34]; also, most MBI studies collect their primary outcome at 3 months postbaseline as most mindfulness interventions span 6 to 10 weeks [7,34]. For this study, we therefore used a medium effect size (*f*=0.25) to conduct an a priori sample size calculation using the software G*Power 3.1.9.3 developed and maintained by researchers at Heinrich Heine University Düsseldorf [35]. The other parameters for estimating the sample size included, a standard type-1 error rate, α=.05, and a low risk of type-2 error, power (1-β)=.95, to detect interaction effects between time points (baseline and 3 months postbaseline) and group (intervention and control) using a repeated measures analysis of variance with correlation among repeated measures assumed to be 0.5 and nonsphericity correction ε=1. The total required sample size reported by G*Power was 54 participants to detect such an interaction effect.

In addition, based on our previous experience with online and in-person MBI trials and previous app-based studies [10,18,20,34,36], we assumed approximately 20% attrition and 10% to 15% probability of missing data. Therefore, we oversampled for this study accordingly. Hence, the final total sample size we aim to recruit in this study is N=74, with n=37 in the immediate intervention arm and n=37 in the waitlist control arm. Please refer to Figure 2 for the study flowchart that describes estimated sample size calculations at each assessment.

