### Data Analysis

Participants will enter data from their home computers or smartphones using the secure REDCap data collection and management system (approved by the University of Calgary and Alberta Health Services). Data will then be transferred into SPSS and or SAS for analysis. Data analyses will utilize linear mixed models (LMM) and intent-to-treat (ITT) principles to assess several planned comparisons across the groups based on identified aims and hypotheses.

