### Hypothesis Testing

#### Hypothesis 1

LMM is a suitable statistical method for this study because of the ability to perform sophisticated statistical imputation of data missing at random in a longitudinal study design. In addition, the LMM also includes mixed effect methods with a random intercept model, which can account for the variances between participants and within participants. Therefore, we plan to use the LMM analyses for testing hypotheses 1 and 2, wherein the LMM will estimate differences between the immediate group and waitlist control group by conducting a group × time interaction analysis with a significance level of α<.05. Each of the LMMs will include fixed effects for time (within-subjects factor) and group (between-subjects factor) and a random effect for the participant. Also, the restricted maximum likelihood estimate method in the LMM will be used to estimate the model parameters and standard errors with a compound symmetry covariance structure to account for the correlation between measurements. Data for testing hypothesis 1 will be C-SOSI total scores and subscale scores for 3 months postbaseline. Within- and between-group differences for the immediate and waitlist groups revealed by the LMMs will be reported with respective *P* values and the specific model effects, *F* (*df*).

#### Hypothesis 2

Similar to hypothesis 1, for hypothesis 2, we will use the same LMMs to test for within- and between-group differences for the secondary outcomes.

#### Hypothesis 3

For hypothesis 3, linear and curvilinear multiple regression models will be used, along with simple Pearson correlations to detect associations between the primary and secondary self-reported outcomes and the exploratory outcomes obtained from the app data.

#### Hypothesis 4

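### The Kenward-Roger correction is made conditional on non-normal data, which it does not remedy; one degrees-of-freedom method should apply to every mixed model (minor)

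*Protocol article*

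**What the plan says.** Under Descriptive Statistics, the article says that "all variables will be checked for normality of distribution", and then that "In case data are nonnormal, the Kenward-Roger correction for degrees of freedom will be applied to the LMM". No other condition for using Kenward-Roger is given, and no other response to non-normality appears in the article.

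Under Hypothesis Testing, the primary comparison is made by "conducting a group × time interaction analysis with a significance level of α<.05". The model has a random participant effect and uses restricted maximum likelihood (REML) to "estimate the model parameters and standard errors with a compound symmetry covariance structure to account for the correlation between measurements". Results are to be given as P values and F statistics with their df. No df method is named for data that pass the normality check. Under Data Analysis, the software is left as SPSS, SAS or both.

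**The concern.** Kenward-Roger answers one question: how much extra uncertainty arises because the variance components were estimated by REML from a limited number of participants? The answer depends on sample size, design and missing-data pattern. It does not depend on whether scores are skewed, and its derivation assumes normal data. Making it the response to non-normality ties it to a condition that it cannot treat.

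Three things follow from the sentence as written.

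- **No working response to skew.** A report that followed the rule could say that non-normality had been corrected when nothing relevant had been done. Skew is plausible for symptom scores in a sample that excludes people with current major depression, but this is an assumption, because the article gives no distribution.
- **A data-dependent df method for the primary test.** The switch is a check with no stated test, threshold or deciding variable. It is described for variables, whereas the model's assumption concerns residuals and random effects.
- **The small-sample correction is optional in a small trial.** The trial needs 54 participants and recruits 74, so a finite-sample method belongs in the model by default.

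**Working it through.** **Inputs.** From Sample Size: f=0.25, alpha 0.05, power 0.95, correlation 0.5, ε=1, two groups, two time points (baseline and 3 months), required N=54, target N=74, about 20% attrition. From Hypothesis Testing: REML, compound symmetry, random participant effect, F with df reported. Assumed here: lognormal skew, monotone dropout reaching 20% by the last visit, and either two visits or the four visits up to 3 months.

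**Step 1. The plan's own figure.** For the group-by-time interaction with m=2 time points, λ = f²·N·m/(1−ρ) = 0.0625 × 54 × 2/0.5 = 13.5, with 1 and 52 df. Power is 0.9501; at N=52 it is 0.9424. The stated 54 is reproduced, and nothing in this point changes it.

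**Step 2. Largest plausible cost of having no finite df.** With compound symmetry and complete data, a p-df interaction test has p(N−2) denominator df. If it is wrongly referred to chi-square with p df (95% points 3.84, 7.81 and 11.07), its true size is P(F(p, p(N−2)) > χ²/p):

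| Test | N=54 | N=74 |
|---|---|---|
| 1 df (two visits) | F(1,52) > 3.84: 5.5% | F(1,72) > 3.84: 5.4% |
| 3 df (four visits) | F(3,156) > 2.605: 5.4% | F(3,216) > 2.605: 5.3% |
| 5 df (six visits) | F(5,260) > 2.214: 5.3% | F(5,360) > 2.214: 5.2% |

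With 20% attrition, 54 × 0.8 = 43.2. Taking 44 completers gives 42 df, and the 1-df figure becomes 5.7%.

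**Step 3. What Kenward-Roger changes, and whether it responds to skew.** A null simulation of the REML compound-symmetry model (3,000 runs per setting, Monte Carlo standard error about 0.4 points) gave these type I error rates for the contrast between baseline and last visit:

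| N, visits, data | z | Satterthwaite | Kenward-Roger |
|---|---|---|---|
| 54, 2, normal | 6.2% | 5.6% | 5.5% |
| 54, 2, skewed | 5.0% | 4.3% | 4.3% |
| 54, 4, normal | 5.5% | 5.3% | 5.3% |
| 54, 4, skewed | 5.7% | 5.5% | 5.5% |
| 74, 2, normal | 6.6% | 6.1% | 6.0% |
| 74, 2, skewed | 4.9% | 4.4% | 4.3% |
| 74, 4, normal | 4.3% | 4.1% | 4.1% |
| 74, 4, skewed | 4.9% | 4.9% | 4.8% |

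The rows scatter around 5%, some by more than two Monte Carlo standard errors. The informative comparison is therefore across columns, where all three methods see the same simulated data. Kenward-Roger and Satterthwaite differ by 0.1 points or less.

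The adjustment itself hardly changes with distribution. At N=54 with two visits, mean df are 45.5 for normal and 45.6 for skewed data, and the standard error is multiplied by 1.0029 and 1.0027. It does change with sample size and design: mean df are about 63 at N=74 with two visits, and about 140 (N=54) and 194 (N=74) with four visits. This confirms that the correction answers sample size and design, not shape.

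**The case against.** The strongest defence is that almost nothing moves. The planned comparison is close to a 1-df contrast: Hypothesis 1 is set at 3 months, and the sample size rests on baseline and 3 months only. Tests over six visits run past the waitlist crossover and belong to the exploratory Hypothesis 4. Results "will be reported with respective *P* values and the specific model effects, *F* (*df"), so a finite denominator df is implied even where none is named. Residual diagnostics and sensitivity analyses are also commonly left to an analysis plan, which is not shown here. All of this stands, and it limits the point to the sentence that the article does contain.

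Three stronger readings are tempting, and the document does not support them.

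- **That the primary test is materially anticonservative.** A reader could refer a Hotelling T² statistic to chi-square and obtain 7.0% (N=54) and 6.4% (N=74) for 3 df, and 8.9% and 7.7% for 5 df. Those figures assume an unstructured covariance. The article fixes compound symmetry, for which the figures are those in Step 2.
- **That data judged normal are analysed with no small-sample df at all.** The article says only when Kenward-Roger is used. It does not say that nothing is used otherwise.
- **That skew would invalidate the test.** With lognormal data the simulated size was 4.3% to 5.5% under Satterthwaite or Kenward-Roger, so harm to type I error is not shown.

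The defence does not rescue the rule itself. It is a positive statement rather than a detail left for later, and it assigns a method to a problem that the method does not address.

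**Conclusion.** The rule is wrong as written, and the severity is minor. Kenward-Roger is not a remedy for non-normality, so the article's one stated response to non-normal data is ineffective. The same sentence makes the df method of the primary test depend on an undefined check of the variables.

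Under the specified compound symmetry and complete data, the worst case of no finite df gives a true size of about 5.2% to 5.5% at N=54 to 74 (5.7% for the 1-df test at 42 df). The actual effect is probably smaller, since F tests with df are promised. The choice between Kenward-Roger and Satterthwaite moves type I error by about 0.1 points or less. These sizes rest on compound symmetry holding and, for the simulated values, on the assumed skew, dropout pattern and visit numbers. The design figures of 54 and 74 are untouched.

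**What to change.** Replace the sentence under Descriptive Statistics with wording such as: *Kenward-Roger degrees of freedom are used in all linear mixed models, regardless of distribution. Normality is judged on model residuals. If residuals are clearly skewed, the primary 3-month contrast is repeated as a sensitivity analysis on a transformed scale, or with a bootstrap or permutation P value.*

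Satterthwaite would serve equally well here, provided that one method is named in advance for every model. Because the article says that "Data will then be transferred into SPSS and or SAS for analysis", naming the package for the primary analysis at the same time would settle the matter.

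The cost is a short rewrite of one sentence. Sample size, data collection and trial conduct do not change, and the skewness analysis is run only if the residuals call for it.

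### Baseline characteristics entered as main-effect covariates would do almost nothing for the group × time test that decides Hypotheses 1 and 2

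*Protocol article*

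**What the plan says.** Under Descriptive Statistics the protocol article states: "Potential treatment moderators of age, sex, cancer type, cancer stage, and chemotherapy regimen will also be included as possible covariates". The operative words, "will also be included as possible covariates", give no form of entry. The same paragraph says the sample description will "check for group differences between groups using Chi-squared and" t tests.

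Under Hypothesis Testing, Hypothesis 1, the model for Hypotheses 1 and 2 estimates arm differences "by conducting a group × time interaction analysis with a significance level of α<.05". On its terms the article says: "Each of the LMMs will include fixed effects for time (within-subjects factor) and group (between-subjects factor) and a random effect for the participant". Restricted maximum likelihood is used to "estimate the model parameters and standard errors with a compound symmetry covariance structure". No covariate term appears in that description, and group × time is the only interaction named. On the data used: "Data for testing hypothesis 1 will be C-SOSI total scores and subscale scores for 3 months postbaseline". On reporting: "Within- and between-group differences for the immediate and waitlist groups revealed by the LMMs will be reported".

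Under Sample Size the plan expects about 20% attrition and a 10% to 15% probability of missing data, with a target of 74 participants.

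**The concern.** The two sections do not work together on their ordinary reading. Group × time is a within-person quantity: how much more one arm changed than the other. A characteristic that stays fixed over time, added as a main effect, explains differences between people in level. It does not explain differences in change. The random intercept already absorbs those differences in level, so the covariate has almost nothing left to do for the tested term.

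What is at stake is the use made of five named prognostic factors in a sample that the Limitations section itself describes as highly variable. If they are meant to sharpen or adjust the primary test, they will not do so in this form. They would still alter the between-group differences that the plan also reports. Covariates could then visibly change one reported contrast while leaving the P value that decides the hypothesis almost untouched.

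**Working it through.** **1. The plan's own figure.** Inputs from Sample Size: f = 0.25, α = 0.05, power 0.95, two groups, m = 2 time points, ρ = 0.5, ε = 1. For the interaction, λ = f²·N·m/(1 − ρ) = 0.0625 × 54 × 2/0.5 = 13.5 on 1 and 52 degrees of freedom. This gives power 0.9501; N = 52 gives 0.942. The stated 54 reproduces. No covariates enter it.

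**2. Why main effects cancel.** With two visits and complete data, write the score of person i at visit t as

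Y_it = μ + a_i + βx_i + γg_i + τt + δ(g_i × t) + e_it, with t = 0 or 1.

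The change is Y_i1 − Y_i0 = τ + δg_i + (e_i1 − e_i0). The random intercept a_i, the covariate term βx_i and the group main effect all drop out. The estimate of δ is the difference in mean change between arms, and its standard error depends only on the spread of the changes. Neither involves x. With more visits and compound symmetry the same holds for every within-person contrast.

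**3. Size with dropout.** Simulated trials had N = 74, ρ of about 0.5, a group × time effect of −0.5, and 200 runs per row. The covariate effects are assumptions: six covariate terms act on level, one of them also acts on change, and dropout depends on that one. Shifts are absolute changes in the group × time estimate against the model without covariates, in units of the SD without covariates.

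| Visits | Dropout | Main effects: mean shift (max) | SE ratio | Mean SE without covariates | Covariate × time: mean shift |
|---|---|---|---|---|---|
| 2 | 0% | below 1e-14 | 1.000 | 0.251 | 0.096 |
| 2 | about 20% | 0.031 (0.19) | 0.998 | 0.273 | 0.108 |
| 2 | about 30% | 0.037 (0.18) | 0.996 | 0.285 | 0.117 |
| 4 | 0% | below 1e-14 | 1.000 | 0.239 | 0.065 |
| 4 | about 20% | 0.018 (0.07) | 0.998 | 0.260 | 0.085 |
| 4 | about 30% | 0.023 (0.10) | 0.997 | 0.271 | 0.092 |

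At about 20% dropout the mean shift is 0.031/0.273 = 11% or 0.018/0.260 = 7% of a standard error. The zero in the complete-data rows does not depend on the assumed covariate effects. The last column shows that covariate × time terms act on the tested term; it does not show that they improve it.

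In the same runs, main-effect covariates moved the between-group contrast at the last visit by 0.10 to 0.13 SD on average (maximum 0.53), even with complete data.

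**4. What the alternatives offer.** For score variance σ², the variance of a change is 2σ²(1 − ρ) = σ² at ρ = 0.5. The variance of the 3-month score given baseline is σ²(1 − ρ²) = 0.75σ². The ratio of standard errors is √0.75 = 0.866, a reduction of about 13%. At N = 74 with complete data this is √(4/74) = 0.232 against 0.866 × 0.232 = 0.201, in SD units. Simulation gave 12 to 14%.

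For covariate × time the gain depends on the covariate. One assumed strong covariate (correlation 0.20 with baseline and 0.45 with the 3-month score, 30% missing) took the sampling SD of the estimate from 0.268 without covariates to 0.253. The same covariate as a main effect gave 0.263. Simulation with 5 to 10 covariate terms by time at N = 58 to 74 showed no gain, and up to 11% larger sampling SD.

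**5. The baseline tests (side point).** The SD of a chance imbalance is √(4/74) = 0.232 SD. Reaching P < .05 takes an imbalance of 0.46 SD. Imbalances above 0.3 SD arise by chance in about 20% of trials.

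**The case against.** The strongest reply is that the article never says how the covariates enter. It calls them potential moderators, which may point to interaction terms, and such terms do change the estimate. Exact covariate form is also commonly left to an analysis plan that is not shown. It stands that main-effect entry is an inference. The article does, however, name the covariates, the model and the deciding contrast, and covariates ordinarily means main effects. The moderator reading does not settle the matter: with covariate × group × time terms, the group × time coefficient applies only at particular covariate values, and nothing suggests that this is the intended primary test.

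Four further points stand:

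- The covariates are not inert for everything. With incomplete data the tested term moves slightly, and the between-group contrasts move noticeably. Hypothesis 1 is itself worded as a comparison at 3 months.
- A reader might infer that the trial would present as adjusted a result that is not. The document never calls the primary result adjusted and never presents the covariates as a remedy for imbalance.
- A reader might infer that the baseline tests choose the covariates. No such rule is stated.
- A reader might infer that chance imbalance invalidates the primary test. It does not: randomization keeps the unadjusted test valid, and its standard error already allows for chance imbalance.

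**Conclusion.** The point holds in a limited form. If the five listed characteristics enter as main effects, they have no effect on the group × time estimate or standard error with complete data. At about 20% dropout the average effect is about 0.02 to 0.03 SD, roughly a tenth of a standard error. The exact result needs only time-invariant covariates, a random intercept with compound symmetry, and complete data. The dropout figures also rest on the assumed covariate effects and dropout mechanism.

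To say that the covariates cannot affect the result would go too far, because the plan expects incomplete data and the form of entry is not stated. The consequence is a missed gain in precision and an unclear role for the covariates; the primary test remains valid. The larger available gain comes from conditioning on the baseline score, about 12 to 14% of the standard error at ρ = 0.5. The baseline significance tests are a minor matter with no stated effect on the primary result.

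**What to change.** In Descriptive Statistics and Hypothesis Testing:

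- **Preferred.** Estimate the 3-month arm difference for each outcome from a model of post-baseline scores that includes the baseline score of the same outcome. Enter any prespecified covariates in that model, where they act directly on the arm difference.
- **If group × time is kept.** State that any covariate meant for adjustment enters as covariate × time. Limit these to a few factors with collapsed categories (for example, chemotherapy yes or no), because many terms cost precision at 74 participants or fewer.
- **Moderation.** If it is meant, give covariate × group × time as a separate analysis.
- **Baseline characteristics.** Show them by arm descriptively and drop the chi-squared and t tests.

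The cost is analysis wording only. Baseline scores are collected before randomization, so no new data are needed. A participant with no post-baseline score contributes no outcome to the preferred model, and the intent-to-treat text should say how such participants are handled.

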### Hypothesis Testing

#### Hypothesis 1

LMM is a suitable statistical method for this study because of the ability to perform sophisticated statistical imputation of data missing at random in a longitudinal study design. In addition, the LMM also includes mixed effect methods with a random intercept model, which can account for the variances between participants and within participants. Therefore, we plan to use the LMM analyses for testing hypotheses 1 and 2, wherein the LMM will estimate differences between the immediate group and waitlist control group by conducting a group × time interaction analysis with a significance level of α<.05. Each of the LMMs will include fixed effects for time (within-subjects factor) and group (between-subjects factor) and a random effect for the participant. Also, the restricted maximum likelihood estimate method in the LMM will be used to estimate the model parameters and standard errors with a compound symmetry covariance structure to account for the correlation between measurements. Data for testing hypothesis 1 will be C-SOSI total scores and subscale scores for 3 months postbaseline. Within- and between-group differences for the immediate and waitlist groups revealed by the LMMs will be reported with respective *P* values and the specific model effects, *F* (*df*).

#### Hypothesis 2

Similar to hypothesis 1, for hypothesis 2, we will use the same LMMs to test for within- and between-group differences for the secondary outcomes.

#### Hypothesis 3

For hypothesis 3, linear and curvilinear multiple regression models will be used, along with simple Pearson correlations to detect associations between the primary and secondary self-reported outcomes and the exploratory outcomes obtained from the app data.

#### Hypothesis 4

The short-term (2 weeks and 1 month postbaseline), medium-term (3 and 6 month postbaseline), and long-term (6 and 12 month postbaseline) longitudinal changes in the primary and secondary outcomes will be determined using the LMM quadratic model regressions. To account for the correlation between measurements, the restricted maximum likelihood estimate method in LMM will be used to estimate the model parameters and standard errors with a compound symmetry covariance structure. In addition, analyses with data nesting within participants will also be conducted that will control for the invariant part of each participant’s scores. The LMM regression weights (β) as well LMM regression coefficients will be reported along with a quadratic regression graph including all time points of data collection.

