### Objectives and Hypotheses

#### Objective 1: Primary Outcome

The first objective is to evaluate the efficacy of the *Am* app–based MBCS program to relieve symptoms of stress (primary outcome).

*Hypothesis 1:* Compared with controls, the *Am* app–based MBCS program participants will report significantly less symptoms of stress at 3 months postbaseline (primary outcome) assessment.

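### The group-by-time test of Hypothesis 1 is unbiased for the 3-month effect but inefficient: no baseline constraint or baseline covariate is named, and the model's visits and deciding contrast are left open

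*Protocol article*

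**What the plan says.** Under Objective 1, Hypothesis 1 states that app participants, compared with controls, "will report significantly less symptoms of stress at 3 months postbaseline (primary outcome) assessment".

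Under Hypothesis Testing, the protocol article says that the linear mixed model will compare the arms "by conducting a group × time interaction analysis with a significance level of α<.05". The model has fixed effects for time and group, a random participant effect, REML estimation and compound symmetry. The data named for Hypothesis 1 are the C-SOSI scores at 3 months. Within- and between-group differences will be reported with F statistics and P values. Hypothesis 2 uses the same models.

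The Sample Size section powers the trial "to detect interaction effects between time points (baseline and 3 months postbaseline) and group (intervention and control"), with "correlation among repeated measures assumed to be 0.5 and nonsphericity correction ε=1". The Randomization section places allocation after the baseline assessment. The Descriptive Statistics section lists possible covariates (age, sex, cancer type, stage and chemotherapy regimen); baseline C-SOSI is not among them.

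**The concern.** Two things are at issue.

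The first is efficiency. Because allocation follows the baseline assessment, the arms have the same expected baseline mean. A model that leaves the baseline group difference free, and then tests change from it, spends information on a quantity that the design already fixes at zero. Constraining the baseline means to be equal, or using baseline C-SOSI as a covariate, recovers that information.

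The second is clarity of the decision rule. A group × time interaction cannot be fitted to 3-month scores alone. The Hypothesis Testing section does not say which other visits enter, or which contrast gives the P value for Hypothesis 1. With two visits the interaction has one degree of freedom and targets the 3-month effect. With more visits, the same words describe an omnibus test that responds to a difference in change at any visit.

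**Working it through.** **Inputs.** From Sample Size: "a standard type-1 error rate, α=.05"; "a low risk of type-2 error, power (1-β)=.95"; f = 0.25; correlation ρ = 0.5; ε = 1; two groups and two visits; N = 54 before inflation to 74. Allocation is 1:1 (Study Design). Equal variance σ² at each visit is assumed, as under the plan's compound symmetry. n is the number per arm.

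**Step 1: reproduce the plan's figure.** For the within-between interaction in G*Power, λ = N·f²·m/(1−ρ) = 54 × 0.0625 × 2 / 0.5 = 13.5, with 1 and 52 degrees of freedom. Power is 0.9501 at N = 54 and 0.9424 at N = 52. The 54 is reproduced, so the test that was powered is the 1-df, two-visit interaction.

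**Step 2: variance of each contrast, in units of 2σ²/n.**
- Interaction (difference in change): 2(1−ρ) = 2 × 0.5 = 1.00.
- Between-group difference at 3 months from the same unconstrained model: 1.00.
- Difference at 3 months with baseline constrained equal, or as a covariate: 1−ρ² = 1−0.25 = 0.75.

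The reduction from the first to the third is 1−(1+ρ)/2 = (1−ρ)/2 = 25% at ρ = 0.5. The standard error ratio is √0.75 = 0.866, which is 13% smaller. The equivalent sample size ratio is 1/0.75 = 1.33.

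**Step 3: range over ρ.** Only 0.5 is given in the protocol; the other values are assumptions.

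| ρ | Interaction | Baseline constrained or adjusted | Variance reduction | SE ratio | N ratio |
|---|---|---|---|---|---|
| 0.3 | 1.40 | 0.91 | 35% | 0.806 | 1.54 |
| 0.5 | 1.00 | 0.75 | 25% | 0.866 | 1.33 |
| 0.7 | 0.60 | 0.51 | 15% | 0.922 | 1.18 |
| 0.8 | 0.40 | 0.36 | 10% | 0.949 | 1.11 |

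**Step 4: source of the gain.** Generalised least squares under compound symmetry with ρ = 0.5 and complete data gives the same 1.00, 1.00 and 0.75 for models with two, four and six visits. The gain comes entirely from how baseline is handled. Replacing the interaction by the plain 3-month contrast in the unconstrained model gains nothing at ρ = 0.5. With complete data the 2- and 4-week scores add no precision either; their use is to inform 3-month scores that are missing.

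**Step 5: effect on the plan's own power.** With variance factor 1.00, λ = d²N/4, so λ = 13.5 at N = 54 means d = √(4 × 13.5/54) = 1.0. At that effect, power at N = 54 is 95.0% for the interaction and 98.6% with baseline adjusted. The N for 95% power falls from 54 to 42.

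**Step 6: degrees of freedom.** With two arms and m visits the interaction has m−1 degrees of freedom: 1 for baseline and 3 months, 3 if the 2- and 4-week visits enter, and 5 if all six visits enter. The last would include the 6- and 12-month scores, collected after the waitlist arm crosses over.

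**The case against.** The strongest reply is that nothing here is invalid. With two visits and randomised arms, the interaction has the same expectation as the 3-month between-group difference, and it is the test that the sample size was computed for. This stands. A reader might infer that the interaction asks a different question from Hypothesis 1, or that the 25% is the price of using an interaction. Neither follows: the two-visit interaction estimates the same effect, and the loss comes only from baseline handling.

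A reader might also infer that the plan could declare Hypothesis 1 supported with no effect at 3 months. With four visits and assumed effects of 0.4, 0.6 and 0 SD at 2 weeks, 4 weeks and 3 months, the omnibus test rejects about 75% of the time at N = 74 and ρ = 0.5. That pattern is invented for illustration. Sample Size points to two visits, Hypothesis Testing names 3-month scores, and the course over all visits is assigned to Hypothesis 4. The calculation shows why the visits must be named, not that the plan intends such a test.

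A third inference is that adjustment would lift power from 56% to 69%. Those figures take d = 0.5 with all 74 participants complete. They belong mainly to a separate problem: the section cites "a similar medium standardized effect size of Cohen *d*=0.5 for stress" but computes with f = 0.25, which in this design is d = 1.0 (Step 5).

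Finally, an article may leave baseline handling to an analysis plan that is not shown, and the covariate list may not be exhaustive. That baseline is an unconstrained response is therefore inferred from the Sample Size section and the stated model terms. This limits certainty. It does not remove the gap in what the article does fix: an interaction test, 3-month data only, and no named contrast.

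**Conclusion.** The point holds as one of efficiency and clarity, and it should be corrected. As stated, the primary test is unbiased for the 3-month effect, but its variance is 1.00 where 0.75 is available at the plan's ρ = 0.5. Adjusting would give 25% less variance and a 13% smaller standard error, equivalent to 33% more participants. The variance reduction runs from 35% at ρ = 0.3 to 15% at ρ = 0.7. These figures assume equal variances, complete data, and a baseline that enters as a response with a free group effect. Separately, the Hypothesis Testing section is incomplete on its own terms: it names one visit for a test that needs at least two, and does not identify the deciding contrast. The documents do not show that the sample size calculation is undermined by this choice of test.

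**What to change.** State one primary test: the 1-df between-group contrast in C-SOSI total score at 3 months, reported with its 95% CI. Take it from a linear mixed model with categorical time (baseline, 2 weeks, 4 weeks, 3 months) and group × time, with baseline means constrained equal across arms. Alternatively, keep only the post-baseline scores as outcomes and enter baseline C-SOSI as a covariate. Exclude the visits after the waitlist arm crosses over from this model. Including the 2- and 4-week scores lets them inform missing 3-month scores, which matters because the plan expects about 20% attrition and 10% to 15% missing data. Use the same model for Hypothesis 2, with each outcome's own baseline.

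The cost is a change of wording in the analysis plan and a few lines of model code. No new data are needed.
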